### Participants

Eighty participants will be recruited and randomly allocated, with half of the consecutive qualifying cases being assigned to MST-PSB and the other half to MAU.

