### Sample size and power calculation

It is estimated that the Brandon Centre will have approximately two eligible cases per month, where referrals are obtained from a minimum of four boroughs, which would result in 72 cases randomized into the trial over the 3-year recruitment period. Five more boroughs are set to join the trial, resulting in nine boroughs in total; it is predicted that this will result in 34 eligible referrals per year, to give a total of approximately 102 cases randomized over 3 years.

Effect size has been estimated on the basis of the available data from a recent MST intervention study of sexual offenders in the United States [46]. As only summary statistics were available, 95 % confidence intervals for effect size were used and the lower limit chosen in a conservative approach. On the basis of the number of participants in the two groups who moved from offender to non-offender status during the follow-up period, the highly significant effect of treatment (*P* < 0.001, Fisher’s exact test) is 0.32 to 0.49 (Cramer, a medium to large effect). In the current study, non-offender status is defined as no arrest leading to conviction over the follow-up period, based on police computer records. We expect to achieve the lower end of the effect size range, given that the trial is mounted independently (although under the supervision) of the development team and involves the transportation of the clinical methodology across national boundaries, healthcare systems and cultures. A sample size estimate to give 80 % power based on the lower estimated effect size of 0.32 suggests 56 participants in a two-group design. Figure 1 shows the expected flow of participants from recruitment through to the end of the study.

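### The stated 56 participants do not give 80% power at a Cramer effect of 0.32: with alpha, sidedness and test unstated, a 5% chi-square test needs 77 two-sided or 61 one-sided

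*Protocol article*

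**What the plan says.** All of the following is in the protocol article.

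- **Effect (Sample size and power calculation).** The effect comes from a United States study of MST in sexual offenders. It is based on the numbers who moved from offender to non-offender status, and it "is 0.32 to 0.49 (Cramer, a medium to large effect"). The lower limit is chosen as the conservative option.
- **Outcome (same section).** For this trial, "non-offender status is defined as no arrest leading to conviction over the follow-up period".
- **Sample size (same section).** 80% power, "based on the lower estimated effect size of 0.32 suggests 56 participants in a two-group design". No alpha, sidedness, test or allowance for loss is given with it. The words "Fisher’s exact test" appear only for the source study's result.
- **Planned size (Participants).** "Eighty participants will be recruited and randomly allocated". Allocation is 1:1 (Randomization and procedures to minimize bias).
- **Forecasts (Sample size and power calculation).** About two eligible cases a month from a minimum of four boroughs, "which would result in 72 cases randomized into the trial over the 3-year recruitment period". With five more boroughs, nine in all, the forecast is "34 eligible referrals per year, to give a total of approximately 102 cases randomized over 3 years".
- **Borough counts.** Five in the Abstract, five localities in The current trial, at least five in Study setting, four rising to nine in the sample size section, and four under Screen 1.

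**The concern.** The section fixes the effect, the power and the answer, so the answer can be checked, and it does not follow on the scale that the section names. A reader who sees 56 required and 80 planned will credit the trial with a reserve of 24 participants (24/56 = 43%). The trial is also meant to inform the power calculation for a full efficacy trial. If the same method were carried forward, that trial would be sized too small.

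The forecasts have a separate weakness. In both, the number eligible becomes the number randomized with no step for refusal. Yet the article's section on the current trial expects that families may hesitate to take part, and treats recruiting an adequate sample as a feasibility question.

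**Working it through.** **Inputs from the article.** V = 0.32, so V² = 0.1024; power 80%; binary outcome; two groups at 1:1; stated size 56; planned size 80.

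**Assumption.** Alpha is 5%. The article does not state it, so both sidednesses are shown.

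**1. Recovering 56.** Read 0.32 as a point-biserial correlation. The standardized difference is d = 2 × 0.32 / √(1 − 0.1024) = 0.6755.
- One-sided normal formula: n per arm = 2 × (1.645 + 0.842)² / 0.6755² = 27.1, so 28 per arm and 56 in total.
- One-sided noncentral t: 56 is the smallest total that reaches 80% (power 80.3%).
- Two-sided: 70 by the normal formula and 71 by noncentral t. Power at 56 is 69.9%.

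So 56 fits a one-sided 5% t-test for a continuous outcome.

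**2. The scale that the article names.** For a 2×2 table with 1 degree of freedom, N = (z_alpha + z_power)² / V².
- Two-sided 5%: (1.960 + 0.842)² / 0.1024 = 7.849 / 0.1024 = 76.6, so 77.
- One-sided 5%: (1.645 + 0.842)² / 0.1024 = 6.183 / 0.1024 = 60.4, so 61.

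**3. Power on that scale**, Φ(0.32√N − z_alpha):

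| N | Two-sided 5% | One-sided 5% |
|---|---|---|
| 56 | 66.8% | 77.3% |
| 72 | 77.5% | – |
| 77 | 80.2% | – |
| 80 | 81.7% | 88.8% |

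With 56 participants, 80% power two-sided would need an effect of 2.802/√56 = 0.374, not 0.32.

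**4. Other routes tried.**
- Fisher's z transformation gives 75 two-sided and 60 one-sided. Without its added 3, the one-sided figure is 56.2, which rounds up to 57.
- The two-proportion formula without continuity correction gives 76 two-sided and 60 one-sided.
- The arcsine formula needs a mean event rate that the article does not give. As that rate is varied from 50% down to 12%, it gives 74 down to 59 two-sided and 58 down to 46 one-sided. The one-sided value passes 55.9 at an assumed 25%. That match rests on two unstated choices, one of them an event rate, so it cannot be read from an effect of 0.32 alone.

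**5. Margin.** 80 − 56 = 24 as the article reads. 80 − 77 = 3 under a two-sided 5% chi-square test.

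**6. Forecasts.** 2 × 36 = 72 and 34 × 3 = 102, so both take every eligible case as randomized. Randomizing 80 of 102 needs 80/102 = 78% to consent.

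**The case against.** The best defence is that the article never claims a two-sided 5% test. Alpha and sidedness may stand in the full protocol or analysis plan, and 56 is reproducible under a one-sided calculation. This stands in part: 77 depends on the two-sided convention, and the missing alpha is not itself the fault. But a one-sided test does not rescue 56 on the Cramer scale at 5%, because it needs 61. Recovering 56 from the stated effect alone also requires a continuous-outcome test for a binary outcome.

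The second defence is that little turns on the figure. This also stands in part. The planned 80 exceeds 77. The Statistical analysis plan section describes the primary outcome by Kaplan-Meier curves and group proportions, and names no between-group test for it. Elsewhere, however, the article presents the trial as a test of effectiveness, so a power statement should be right.

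A reader might infer more than the article supports:
- **That the forecast reaches only 72 of 80.** That is the four-borough scenario. The next sentence forecasts about 102, and at least five boroughs is compatible with nine.
- **That refusals erode power.** Consent precedes randomization, and the 80 are those randomized. Refusal lengthens recruitment and does not lower power among the 80.
- **That there is no room for loss.** The conviction outcome comes from police records, not from interview attendance, and the flow figure is not shown and may carry allowances for refusal or loss.
- **That power should be restated for Fisher's exact test.** That test is named only for the source study, and its power depends on event rates that the article does not give.

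**Conclusion.** The point holds with moderate weight. On the Cramer/chi-square scale that the article cites for a binary outcome, 56 participants do not give 80% power at 5%. The requirement is 77 two-sided (56 gives about 67%) or 61 one-sided (56 gives about 77%). The 5% level is an assumption, and the choice between 77 and 61 rests on a sidedness that the article leaves open. That 56 falls short on this scale does not depend on which sidedness is taken.

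It does not follow that the planned trial is too small. At 80 randomized with complete data, two-sided power is about 82%. What is wrong is the stated requirement and the reserve that it implies.

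The forecast point is secondary. Counting all eligible cases as randomized is optimistic given the article's own doubts about consent, and the borough counts need reconciling. Neither shows that 80 is out of reach.

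**What to change.** Text only, with no added enrolment:

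1. State the alpha, sidedness and test behind the sample size.
2. Replace 56 with the figure that matches them on the Cramer scale. Under the conventional two-sided 5% chi-square test this is 77 in total.
3. State that the planned 80 gives about 82% power at an effect of 0.32 under that test with complete data, a margin of 3 over the requirement.
4. Restate each forecast as eligible cases multiplied by an assumed consent rate, and note that 80 from 102 eligible needs about 78%.
5. Reconcile the borough counts (five, at least five, four rising to nine), saying which holds at which stage.

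The cost is a less favourable power statement. The planned 80 and the descriptive analysis stay as they are.

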**Fig. 1 Fig1:**
[figure not shown]
CONSORT flow diagram of progress through the phases of recruitment and treatment in the STEPS-B trial of multisystemic therapy for youth with problem sexual behaviour

### Eligibility criteria

Participants will be adolescents who meet the criteria for ‘high risk’ of requiring out-of-home care, specifically when this risk is associated with problem sexual behaviour.

#### Inclusion criteria

Inclusion criteria are as described below:Young people aged 10 to 17 years oldSufficient family involvement for MST-PSB to be applied: either living in the parental home, in long-term foster care, or in short-term out-of-home placement but family reunification is imminent (within 30 to 60 days)The young person and family are not already engaged in a problem sexual behaviour-specific treatmentProblem sexual behaviour within the past yearRisk of custody or out-of-home placementRisk of reoffendingDisplaying aggression at home, at school or in the community.

#### Exclusion criteria

Exclusion criteria are as follows:Young person is living independently or a primary caregiver cannot be identifiedThe sexual offence is under police investigation at the time of referralThe primary reason for referral is related to suicidal, homicidal or psychotic behavioursCaregiver persistently denies that the young person has engaged in problematic sexual behaviourYoung person has pervasive developmental delaysYoung person has generalized learning problems (clinical diagnosis) as indicated by IQ <65Young person has severe substance misuse as the primary presenting problem.

### Recruitment and baseline procedures

The authors have developed a multiple gating procedure for recruitment, based partly on the experience of the largest adolescent mental health trial to date evaluating standard MST for youth displaying conduct problems [28], which, similarly, recruited complex families with multiple needs. Using this procedure, decisions about eligibility are made at three points: first, by a telephone discussion between the referrer and the MST-PSB supervisor; second, through discussions between the MST supervisor and the research team, based on information gathered from the referral form; and third, through discussions between the MST supervisor and the research team after having received additional information from an introductory home visit attended by the MST-PSB supervisor and an RA, with the purpose of explaining the rationale for the research trial and answering any questions about the MST-PSB and MAU services potentially available to the family.

In order to maximize recruitment and to ensure that our planned sample size is achieved, research personnel are involved in several activities with different parts of the system that may influence recruitment. Specifically, a member of the research team attends service team meetings and multi-agency panels that review potential referrals in the different boroughs, and there is regular contact with service leads and managers, which will influence the visibility and importance of the trial within services. Finally, ongoing service and agency awareness is complemented by ongoing presentations (for example, to youth offending evidence-based practice and judicial forums), a quarterly newsletter sent to all potential referrers, and an active website, which provides information for service teams about how to make a referral, a referral leaflet, a description of MST-PSB and the STEPS-B trial, and a ‘frequently asked questions’ section for young people, parents/carers and professionals.

#### Screen 1

Referrals are anticipated from youth offending services, CAMHS, social care and education services (see Fig. 1). Prior to the clinical trial, the MST-PSB team established close working relationships with the four referring boroughs through presentations, screening referrals, working with families and developing relationships with other service providers for youth displaying problem sexual behaviour.

Before a referral form is submitted, the potential referrer will complete a telephone case consultation with the MST-PSB supervisor. As the cohort is not homogeneous, individual cases will often require different levels of support. During the telephone consultation, the MST-PSB supervisor will screen the case against the eligibility criteria and begin to plan in parallel with the referrer another potential sexually harmful behaviour intervention, if the case and family are not randomly allocated to MST-PSB.

#### Screen 2

Once a referral has been accepted, the clinical team sends a standard letter to the parents (and separately to the young person if aged 16 or 17), informing them of the trial. In addition, the MST-PSB supervisor contacts the family by telephone to discuss the trial and arrange an introductory meeting.

The introductory meeting takes place at the family home, with the MST-PSB supervisor, senior RA, young person and primary carer(s) present. At this meeting, the nature of and concerns related to the young person’s problem sexual behaviour are reviewed and a credible MAU path (the best alternative treatment at that locality; see below), should the young person not be randomized to receive MST-PSB, is agreed upon by the young person, primary carer(s) and the trial team. Further information is also gathered regarding eligibility, such as agency involvement incompatible with participation in the trial (for example, the family is already engaged in a treatment that would interfere with MST-PSB), potential risk of harm to workers, or whether the young person has generalized learning problems. In the event that the primary carer steadfastly denies that the young person has engaged in problem sexual behaviour, the MST-PSB supervisor will offer a maximum of three sessions to explore the allegations with the primary carer(s), to see whether their position shifts. At the end of the introductory visit, the young person and primary carer(s) are given specifically tailored information outlining the trial, in age-appropriate and culturally appropriate language. The family is given contact details for the RA so that they can contact the RA if they have any further questions.

#### Screen 3 and consent

Unless the family expresses a decision not to participate at the time of the introductory visit, they are given a minimum of 3 days to consider whether they would like to join the clinical trial. If the RA does not hear from the family within the agreed time period, the RA telephones the family, answers any additional questions they may have, and arranges an appointment for a research assessment.

At the research assessment, each young person and primary carer(s) sign informed consent forms agreeing to join the clinical trial, including permission to access the police, correctional and educational databases, which remains in effect for 20 months. For families who sign the consent forms, the RA administers pre-randomization questionnaires and measures are completed during this contact (that is, before group assignment).

Once the young person and family’s eligibility have been confirmed and the instruments completed, the RA contacts the trial centre and relays the family’s randomization details. The clinical team informs the family and referrer of the outcome of randomization within 48 hours of the consent and pre-randomization visit being completed.

Once the family has completed the compulsory instruments to be able to join the trial, the young person is asked whether they would like to take part in the optional Child Attachment Interview (see Measures, below). If the young person and primary carer(s) agree, an additional meeting is arranged within 1 week of the date of randomization. At this additional visit, consent forms are signed by the primary carer(s) and young person and the Child Attachment Interview is conducted.

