The available data on prevalence and the difficulty gaining accurate estimates of incidence and service use suggest that the size of the pool of available participants to recruit into an RCT for problem sexual behaviour is uncertain. Therefore, the success of the trial is likely to depend on efficient identification of potential participants. It will also rely on established systems for providing specialist treatments for adolescent sexual offenders and for managing their mental health needs, given that judicial processes can determine the offenders’ availability for mental health interventions or delay timely provision of treatment. Two recent reviews of the provisions for juvenile sexual offenders in the United Kingdom noted that, despite examples of good practice, services for identifying and intervening with young people displaying problem sexual behaviour are underdeveloped [39]. For example, a recent examination of multi-agency responses to children and young people who sexually offend concluded that identification of young people’s problem sexual behaviour was often subject to disbelief, minimization and denial by professionals and by families; that much work was characterized by poor communication between the relevant agencies, with inadequate assessment and joint planning; and that cases were slow to get to court, on average taking 8 months between disclosure and sentencing, resulting in lengthy periods when little or no work was done with the young person [43]. The findings from this joint government inspection suggest that implementation of the MST-PSB trial will require substantial liaison and problem-solving with all relevant stakeholders to help identify young people who are appropriate for the trial and would benefit from the available interventions, as well as planning to accommodate judicial processes that will impact on the timely provision of both MST-PSB and MAU interventions.

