#### Feasibility outcomes

The feasibility outcomes measure chosen variables that the investigators hypothesize will be related to the effective implementation of MST-PSB in the United Kingdom.

First, it is predicted that specific characteristics of young people referred for displaying problematic sexual behaviour will be more likely to result in these young people being randomized into the trial. The specific characteristics that will be examined include the age of the young person, severity of the young person’s problematic sexual behaviour, source of the referral, and whether or not the young person was involved in judicial proceedings at the time of randomization.

Second, the beliefs and attitudes held by professionals working in the agencies and services that will refer into the trial will be evaluated. The data gathered concerning their beliefs and attitudes will include the degree to which they are supportive of a family-based intervention for a young person displaying problematic sexual behaviour; the degree to which they are in accord with the procedures and demands associated with an RCT research evaluation, including the randomization and its consequences; and the degree to which they view the institutions and agencies that manage young people showing problematic sexual behaviour as able to support an RCT evaluation.

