#### Primary outcomes

The primary outcome is the proportion of documented cases of offending within 20 months of randomization, based on police records supplemented by information obtained from the young person, parents/caregivers and social care services. While this may be only a partial or even an inaccurate reflection of the psychological conditions and social behaviours of the participants, it is the indicator of primary concern for the funders of the programme as, in most cases, this record triggers costly juvenile justice and social interventions. A linked outcome, of similarly high concern to funders of services, is assignment to long-term (3 months or longer) out-of-home placements in specialist residential provision when social services consider that the safety of the participant’s family or community is compromised by the individual, even in the absence of arrest and conviction. This means all participants who are placed into local authority care, are incarcerated, long-term hospitalized or offered residential schooling at any time in the 20 months following randomization will not be considered to have moved from the offending to the non-offending group. This information will be obtained from caregivers and cross-referenced with documented information from the national social care services database to maximize accuracy. The investigators expect this trial to give information on how many young people assigned to MAU and to MST-PSB require specialist residential provision either immediately after intervention or during the follow-up period.

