#### Objective measures

Objective outcomes will be collected from reports of sexual and non-sexual offending behaviour based on police computer records, including details of custodial sentences. These measures will be taken at 6-month intervals, for the 6 months before randomization, the 8 months covering the intervention period (adjusted as MST-PSB lasts on average 5 to 7 months), and 6-monthly until the 20-month follow-up point. The number of records of offending behaviour (count data) will be obtained and 6-month periods free of any offending behaviour will also be recorded (binary data). Records will be obtained from the Police National Computer as well as from the Young Offender Information System database; these records detail information on offences, court appearances, criminal orders, police custody records and arrest rates. Records of school attendance and exclusions will be retrieved from both the schools themselves and the National Pupil Database to assess educational outcomes.

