### Primary outcome

The primary outcome of the proportion of cases where a sexual offence has been incurred during the follow-up period will be described by a Kaplan-Meier graph and summarized by the proportions in each group with a new sexual offence by 20 months. The linked outcome of out-of-home placement will also be described by a Kaplan-Meier graph and summarized by the proportions in each group with out-of-home placement by 20 months. The number of events will be estimated in order to inform power calculations for a fully powered efficacy trial.

For time-to-event offending outcomes, the event rate will be estimated. For continuous secondary outcomes, such as questionnaire data, linear mixed effects models will be fitted in order to estimate the individual-level residual variance.

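### Offending is conviction-based in the power section but offence-based in the outcome and analysis sections; with records ending at month 20, the conviction-based reading would miss late offences and does not date events by offence

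*Protocol article*

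**What the plan says.** All places are in the protocol article. Three sections describe the offending outcome, and they differ.

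- Sample size and power calculation: "non-offender status is defined as no arrest leading to conviction over the follow-up period, based on police computer records".
- Primary outcomes, under Assessments and outcome measures: "The primary outcome is the proportion of documented cases of offending within 20 months of randomization, based on police records supplemented by information obtained"; the added informants are the participant, carers and social care. Conviction is not required.
- Primary outcome, under Statistical analysis plan: sexual offences are "summarized by the proportions in each group with a new sexual offence by 20 months". Conviction is not mentioned, and the event counts are to feed the power calculation of a later full trial.

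On timing, Screen 3 and consent gives "permission to access the police, correctional and educational databases, which remains in effect for 20 months", and Objective measures collects police records "6-monthly until the 20-month follow-up point". The background section on the current trial, citing a joint government inspection of young people who sexually offend, says cases were slow to reach court, "on average taking 8 months between disclosure and sentencing".

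On entry, Exclusion criteria removes a sexual offence under police investigation at referral. Feasibility outcomes lists, among the characteristics to be examined, "whether or not the young person was involved in judicial proceedings at the time of randomization".

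**The concern.** A conviction follows an offence by months. If the event is a conviction and the records stop at the same month as the follow-up, the last part of follow-up can hardly produce events. Months without offending then cannot be told from months whose cases are still before the court. The plan allows for court delay when it discusses timely treatment, but not when it discusses how outcomes are ascertained.

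The same definition has a gap at the other end. It speaks of arrest and conviction over follow-up and does not say when the offence must have been committed, so behaviour from before randomization could count as a failure after it.

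At stake is the main quantitative product of a feasibility trial, the event rate handed to the designers of the full trial.

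**Working it through.** The plan gives no figure for offences lost to court delay, so there is none to reproduce. Its sample size of 56 does not enter this check.

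**Inputs from the article.** Follow-up and last record point: 20 months. Mean delay from disclosure to sentencing: 8 months. Treatment: 5 to 7 months.

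**Assumptions.** Offences occur at a constant rate over months 0–20. The 8-month figure stands in for the time from offence to recorded conviction. It omits any delay from offence to disclosure, which would raise the loss, and it runs to sentencing, which may fall after conviction, which would lower it. Lags of 4 to 12 months are therefore shown as well.

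**Share of offences with a conviction by month 20, for lag L.**
- Fixed lag: (20 − L)/20. At L = 8 this is 12/20 = 0.60, so 40% are missed, namely every offence after month 12.
- Exponential lag with mean L: 1 − (L/20)(1 − exp(−20/L)). At L = 8 this is 1 − 0.4 × (1 − 0.082) = 0.633, so 37% are missed.

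| Lag (months) | Missed, fixed | Missed, exponential |
|---|---|---|
| 4 | 20% | 20% |
| 6 | 30% | 29% |
| 8 | 40% | 37% |
| 10 | 50% | 43% |
| 12 | 60% | 49% |

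**From offences to participants.** The outcome is the proportion of participants with any event, and someone with an earlier convicted offence is already counted. If a proportion p truly offends at a constant rate and a share c of offences is captured, the recorded proportion is 1 − (1 − p)^c. With c = 0.60:
- p = 0.05: 1 − 0.95^0.6 = 0.030, a relative loss of 39%.
- p = 0.14: 1 − 0.86^0.6 = 0.087, a relative loss of 38%.
- p = 0.46: 1 − 0.54^0.6 = 0.309, a relative loss of 33%.

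The first two values of p are the ends of the sexual reconviction range in the Background. The third is the usual-services sexual re-arrest proportion in the US efficacy trial. They serve only as illustrative 20-month offence proportions. The participant-level loss stays below 40% and shrinks as reoffending becomes more common.

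**Time after treatment.** The plan offers 20 − 7 = 13 to 20 − 5 = 15 months. With an effective cut-off at month 12, 12 − 7 = 5 to 12 − 5 = 7 months remain.

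**When records would be complete.** With a fixed 8-month lag, at month 20 + 8 = 28.

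**Offences before randomization.** No arithmetic is possible, because the article does not say how many participants will have open cases. On the text alone, the investigation exclusion does not reach cases already charged, offences disclosed later, or non-sexual offences. The power section does not exclude a later conviction for any of these.

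**The case against.** The strongest reply is that conviction appears as a requirement only in the power section. The outcome and analysis sections count offences, and the records described under Objective measures include offences, arrests, court appearances and custody. On that reading an offence in month 15 can be counted by month 20 without a verdict. This stands, and it makes the loss conditional. It does not settle the matter: the power section holds the only explicit definition of non-offender status, and the Primary outcomes section relies on that classification when it says that placed participants have not moved into the non-offending group. No section says whether a late offence without a conviction counts.

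Second, the consent wording might limit the period that the records cover rather than the last date of access. The text does not decide this. Coverage is the less natural reading, since Objective measures needs 6 months before randomization plus 20 after, or 26 in all. Either way, the last record point is month 20.

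Third, a reader might infer that convictions early in follow-up would mostly concern earlier behaviour. The article does not support this. It gives no number, excludes sexual offences under investigation at referral, and uses wording in the outcome and analysis sections that points to dating by offence. Judicial involvement is listed only as a possible predictor of being randomized, not as a stated feature of those enrolled. What remains is a risk from unclear dating.

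Fourth, a reader might infer lost power or misplaced Kaplan-Meier times. The stated analysis of this outcome is descriptive, with no test between arms, and it does not date events by conviction.

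**Conclusion.** The point holds conditionally. The article gives incompatible accounts of when offending counts. Under its only explicit definition of non-offender status, sexual offences disclosed after about month 12 will usually have no conviction on record at month 20. About 37–40% of follow-up offences would be missed at an 8-month lag, and 20–60% across lags of 4 to 12 months. The loss in participants with any event is no larger and probably smaller. The event rate passed to the full trial would be too low by a similar proportion.

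These figures assume that the power-section definition governs, that no records are read beyond month 20, that offences occur at a constant rate, and that the inspection's delay applies to this sample. The article gives no delay for non-sexual offences, so the figures should not be carried over to all offending. Nor do they show that this share of events will be lost whatever definition is used: under the outcome and analysis sections as worded, late offences can be captured. Counting of offences from before randomization is possible under the power-section definition, but its size is unknown.

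**What to change.** Use one event definition in the power, outcome and analysis sections: an offence dated after randomization and by month 20. Count it at arrest or charge, using the police and youth-offending records already to be collected. Exclude offences dated before randomization. Say in the same place whether the event is sexual offending or all offending, and whether an offence known only from the family or social care counts. Report conviction status separately as convicted, pending or dropped.

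The cost is a change of wording and one extra table; no further record access is needed. The downside is small: some counted arrests or charges will not end in conviction. Report the conviction-only proportion as a sensitivity analysis, labelled as immature at month 20.

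If conviction must stay as the endpoint, an option is to extend record access to about month 28 or later for families who consent from now on, still restricted to offences dated in the 20-month window. That costs a consent and ethics amendment and a final extract about 8 months later, and it leaves families already enrolled under the existing permission.
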